### Data Analysis

All analyses will be performed in SPSS (version 29; IBM Corp). A *P* value of .05 or less will be considered statistically significant. The primary outcome is pain severity (BPI-SF) and the primary MOA is ER (DERS). We will examine baseline demographics and study variables descriptively and test for differences between yoga and stretching and strengthening groups. If assumptions are met, a series of 2-sided *t* tests, mixed effects models, and path analyses will test our hypotheses. A mediation path analysis will be conducted examining the indirect path of group and change in ER from baseline to 6 weeks (path a), and change in ER from baseline to 6 weeks and pain severity (BPI-SF) at 12 weeks (path b) controlling for baseline pain severity. The magnitude of indirect path b will be assessed controlling for path a and the direct path between group and change in pain severity at 12 weeks (path c) to test if changes in ER predict subsequent changes in pain severity. Identical models will be created with change in ER from baseline to 12 weeks and pain severity at 3- and 6-month follow-ups. The magnitude of indirect path b will be compared between groups to test if the path between ER and pain severity is greater in the yoga group than in the stretching and strengthening group. If 95% CIs of path estimates do not contain 0, they will be considered meaningful. Finally, a series of moderated mediation path analyses will be conducted, examining the measures of baseline pain sensitivity (QST scores and normalized gene expression values), strength and flexibility, pain interference, and quality of life as moderators of the identical mediation model. All analyses will also be adjusted for important covariates including, but not limited to demographics (eg, biological sex, race, and sex), cohort, instructor, and intervention components (Essential Properties of Yoga Questionnaire) and credibility or perception of success (Credibility Expectancy Questionnaire). Sensitivity analyses will examine whether treatment responders and nonresponders differ significantly in baseline ER abilities. Baseline DERS scores will also be examined as a continuous moderator in main study analyses to establish whether some individuals may enjoy greater benefit from this intervention more than others.

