##### Pain Sensitivity: Peripheral and Central Sensitivity

We will use a comprehensive quantitative sensory testing (QST) battery of mechanical and thermal stimuli [65]: (1) cutaneous mechanical pain sensitivity, involving measures of tolerance, threshold, temporal summation, and after sensations; (2) heat and cold pain sensitivity, involving threshold, tolerance, and ratings of suprathreshold stimuli; and (3) pressure pain thresholds. Interrater reliability of the QST protocol has been reported in several clinical trials, with each individual test achieving a CI of 0.87-0.94 [66,67].

In addition to the QST battery, we will isolate total RNA from whole blood for sequencing at each time point. We will prepare libraries per Illumina standard protocols and sequence RNA on the Illumina HiSeq2500 System (Illumina Inc) to obtain 150 base pair paired-end reads. We will examine how changes in the expression of pain sensitivity genes, as well as the entire transcriptome, differ between the experimental and control group (those with complete data from yoga vs stretching) × sex using statistical modeling and construct a database of gene expression profiles to generate a profile of change in ER, as well as identify novel therapeutic targets for better pain management. We will use a candidate approach to examine genes identified from our preliminary studies, and a hypothesis-generating approach to identify differentially expressed genes.

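### A blanket .05 / 95% CI rule covers the whole-transcriptome comparison and an unnumbered series of moderator models, with no exemption or error control stated for either

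*Protocol article*

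**What the plan says.** Three elements of the protocol article bear on this point.

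- **The decision rules (Data Analysis).** The section opens with "All analyses will be performed in SPSS (version 29; IBM Corp"), and the next sentence makes a P "value of .05 or less will be considered statistically significant". For the path models it adds: "If 95% CIs of path estimates do not contain 0, they will be considered meaningful". Neither rule is limited to a named outcome or family.
- **The gene analyses (Pain Sensitivity: Peripheral and Central Sensitivity).** The trial will examine how "changes in the expression of pain sensitivity genes, as well as the entire transcriptome, differ between the experimental and control group", crossed with sex and restricted to participants with complete data. Candidate genes come from preliminary studies. Beside them stands "a hypothesis-generating approach to identify differentially expressed genes". The stated uses include finding new therapeutic targets. Pain sensitivity is one of the four listed secondary outcomes.
- **The moderator analyses (Data Analysis).** The plan is that "a series of moderated mediation path analyses will be conducted, examining the measures of baseline pain sensitivity (QST scores and normalized gene expression values"), followed by strength and flexibility, pain interference and quality of life. Baseline DERS is a further moderator. The underlying mediation model is fitted for pain at 12 weeks and again at the 3- and 6-month follow-ups.

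The article gives no number of genes, candidate genes or moderator models, and it mentions neither false-discovery nor familywise control.

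**The concern.** A per-test threshold of .05 suits one named primary outcome. It does not suit a screen of thousands of genes, where 5% of the null ones pass by chance, or a long run of interaction models in which any one positive result would be reported as a finding about who benefits. The 95% CI rule repeats the same per-test error rate for paths.

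Moderation by sensitization is a stated objective, and the gene results are meant to point to therapeutic targets. Neither appears under the article's Exploratory Variables heading. If the published rule is followed, the list of significant genes could consist largely or wholly of chance results, and a reader would have no stated error rate by which to judge it or a moderator claim. Later work on yoga and pain could then be directed by noise.

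**Working it through.** The article states no error rate or test count for these families, so there is no figure to reproduce. The check asks what the stated rule implies.

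**1. Genes.** The only input from the document is the threshold, .05. The number of expressed genes, G, is an assumption.

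Expected false positives per tested term, if no gene differs = G × .05.

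| G (assumed) | One term | Two terms (e.g. group and group × sex) |
|---|---|---|
| 4,000 | 200 | 400 |
| 10,000 | 500 | 1,000 |
| 15,000 | 750 | 1,500 |
| 20,000 | 1,000 | 2,000 |

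Correlation between genes does not change the expectation but widens the spread. In 300 simulated null data sets with 15,000 genes, the 5th to 95th percentile range was 701 to 795 with independent genes and about 280 to 1,800 at a pairwise correlation of 0.3. In the same simulations, Benjamini-Hochberg at 5% declared any gene at all in 3% to 6% of data sets, over correlations of 0 to 0.3.

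**2. Moderators.** The count is inferred from the measures listed under Secondary Outcomes and Data Analysis:

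- QST: 4 mechanical (tolerance, threshold, temporal summation, after sensations) + 6 thermal (heat and cold, each with threshold, tolerance and suprathreshold rating) + 1 pressure = 11
- Strength: grip, prone bridge, supine bridge = 3
- Pain interference = 1
- SF-36 subscales = 8
- Baseline DERS = 1

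Total: 11 + 3 + 1 + 8 + 1 = 24, without genes.

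For k independent tests, the chance of at least one false positive = 1 − .95^k, and the expected number = .05k. For k = 24: 1 − .95^24 = .71, with 24 × .05 = 1.2 expected. If the model is repeated over three time windows, k = 72: 1 − .95^72 = .975, with 3.6 expected.

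These measures are plausibly correlated, so the same quantity was simulated with 40,000 draws of equicorrelated z statistics:

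| Correlation | k = 24 | k = 72 |
|---|---|---|
| 0 (formula) | 71% | 97.5% |
| 0.3 | 60% | 89% |
| 0.5 | 46% | 71% |
| 0.7 | 31% | 46% |

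The result depends on the count. One test for each of five broad domains (QST, strength, interference, quality of life, DERS) would give 1 − .95^5 = 23% if independent. At the other end, 100 independent tests, as could arise if many single genes were used as moderators, would exceed 99%.

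The moderator figures take one test per moderator at a true 5% error rate. A model that moderates more than one path adds tests.

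**3. Primary test.** Pain severity at 12 weeks is one named outcome at one time point. Its error rate does not depend on how many genes or moderators are tested elsewhere.

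**The case against.** The strongest reply is that the article never says an unadjusted .05 will be used to declare genes. The words about all analyses govern the software, and the threshold is a separate, general sentence. The methods listed after it are t tests, mixed models and path analyses; differential expression is described elsewhere, only as statistical modelling. Adjusted P values can also be judged at .05. Error control for RNA sequencing is the kind of detail an article may leave to an analysis plan that is not shown. One arm of the gene work is openly hypothesis-generating.

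Much of this stands. A reader might infer that hundreds of false gene targets will in fact be declared; the text supports only that this would follow if the general rule were applied literally. A reader might also infer that every gene-expression value enters as its own moderator. The wording allows that, but equally allows a few candidates or a composite profile.

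The reply does not remove the point. The article goes beyond silence: it publishes a criterion without exemption, and for path estimates it publishes an explicit second one. The moderator series, including gene expression values, sits in the same paragraph as both rules and carries no exploratory label. If an unseen plan already specifies FDR control, the published sentence still needs a carve-out to agree with it.

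**Conclusion.** The concern holds in a limited form. The plan fixes a general .05 rule and a 95% CI rule, and leaves the transcriptome comparison and a moderator series of unstated size under them. Taken literally, this means hundreds of expected false genes per tested term for any assumed count of 4,000 or more. It also means roughly a 31% to 71% chance of at least one false moderator per time window, and more if the windows are repeated or single genes are tested. These sizes rest on assumed gene counts, an inferred count of 24 moderators and assumed correlations.

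Three stronger readings are not supported. False moderators are not near-certain on the listed non-gene measures in one time window: that would need roughly 70 or more nearly independent tests, or gene-level moderators. The primary result is not inflated. And real effects would not be lost beyond recovery, since P values and effect sizes can still be ranked and adjusted afterwards. What is missing is a stated error rate for the claims the trial intends to make.

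**What to change.** Amend the wording in the analysis plan, and note the change against the published article:

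1. State that the .05 criterion applies to the primary outcome (BPI-SF severity at 12 weeks) and the primary mechanism (DERS).
2. For transcriptome-wide tests, use Benjamini-Hochberg FDR at 5%, in a count-based model that uses all available samples rather than only participants with complete data. If this needs dedicated software, exempt it from the SPSS sentence.
3. Fix the candidate-gene list before unblinding and apply FDR separately within it.
4. For moderators, either prespecify a short list of sensitization measures, or label the whole series exploratory and report FDR-adjusted values. The choice between these is a design decision for the investigators.

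No new data are needed. The article plans no interim analyses and places the analysis after final data collection, so the change can be made before results are seen. The price is fewer nominal hits.

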### Procedures

#### Randomization and Blinding

Eligible volunteers are scheduled to meet with a study staff member who will follow all informed consent procedures. After written consent is obtained, participants are randomized to the yoga or stretching and strengthening group using a stratified randomization scheme based on biological sex to ensure balance between groups, and the assigned group is known only by the study staff managing the participant and instructor schedules.

We will use blinding whenever possible. Assessments, evaluations, and data analysis will be conducted without the knowledge of participants’ assigned group. We will blind the study personnel to the assigned condition of subjects when conducting data collection by using unique study identification numbers, by following a strict script to refrain from discussing participant activities, and by using different members of the study team to coordinate assigned condition activities and collect data. Deidentified data with codes for assigned condition will facilitate blinded data analysis.

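### Baseline significance tests between randomised arms are uninformative, and the covariate list for all analyses is left open and includes variables tied to the arm

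*Protocol article*

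**What the plan says.** All of this is in the Data Analysis section of the protocol article unless noted.

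- **Baseline tests.** "We will examine baseline demographics and study variables descriptively and test for differences between yoga and stretching and strengthening groups". A P "value of .05 or less will be considered statistically significant", and baseline comparisons are not exempted.
- **Primary outcome.** "The primary outcome is pain severity (BPI-SF) and the primary MOA is ER (DERS").
- **Adjustment.** "All analyses will also be adjusted for important covariates including, but not limited to demographics". The demographics are given only as examples, with sex appearing twice. The list goes on to name "cohort, instructor, and intervention components (Essential Properties of Yoga Questionnaire) and credibility or perception of success (Credibility Expectancy Questionnaire"). What makes a covariate important is not defined, and there is no rule for adding one.
- **Baseline outcome.** The mediation model is fitted "controlling for baseline pain severity". This is not stated for the direct comparison of arms.
- **Randomisation** (Randomization and Blinding). Participants are allocated "using a stratified randomization scheme based on biological sex to ensure balance between groups". The same section plans blinded analysis using coded arms.
- **Exploratory Variables.** Demographics, attendance or home practice, expectancies and substance use are to be examined for their impact on the primary and secondary outcomes.

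**The concern.** There are two separate faults, and neither needs the other.

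First, a baseline test in a randomised trial tests a hypothesis already known to be true if allocation worked. A small P marks a chance difference. A large P does not show that a prognostic variable can be left out of the model. The article gives the tests no other purpose, such as checking the allocation process.

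Second, the covariate list covers all analyses but is not closed. Covariates beyond the named ones could be chosen after the baseline comparison, or after the outcome associations described under Exploratory Variables. Some named covariates are also not baseline characteristics of participants. Instructor follows from the arm, and the Essential Properties of Yoga Questionnaire rates what was delivered. Adjusting the primary comparison for these can remove part of the contrast that the trial is meant to estimate.

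At stake are the precision and the interpretation of the adjusted primary estimate.

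**Working it through.** The article gives no figure on this point, so there is none to reproduce.

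**1. How often a chance difference would be flagged.** For k independent tests at .05, the expected number of false positives is 0.05k and P(at least one) = 1 − 0.95^k.

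| k | expected | P(at least one) |
|---|---|---|
| 5 | 0.25 | 23% |
| 10 | 0.5 | 40% |
| 20 | 1.0 | 64% |
| 30 | 1.5 | 79% |
| 40 | 2.0 | 87% |

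The article does not state k. A count from the Measures and Exploratory Variables sections gives:

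- 11 sensory measures (4 mechanical, 3 heat, 3 cold, 1 pressure)
- 3 strength measures (grip and two bridge positions)
- 8 SF-36 scales
- 2 BPI scores
- DERS and the priming task (2)
- 5 demographics

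That is 11 + 3 + 8 + 2 + 2 + 5 = 31, or about 30, leaving out medical history and gene expression. Sensory measures and SF-36 scales are correlated, so 79% is towards the upper end. It is the chance of one flagged baseline row, not an effect on the primary result.

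**2. What selection by baseline P would do if it were used.** A simulation used assumed inputs:

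- a linear model with five independent baseline covariates, coefficients 0.5, 0.2, 0.2, 0.2 and 0.1
- within-arm outcome variance 1, so residual variance is 1 − (0.25 + 3 × 0.04 + 0.01) = 0.62
- 102 per arm, or 82 per arm (about 20% loss: 102 × 0.8 = 81.6)
- 5,000 replicates with no effect, and 2,000 at d = 0.4

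| Approach | Type I error, 102 / 82 per arm | Power, 102 / 82 per arm |
|---|---|---|
| Unadjusted | 4.9% / 4.9% | 81% / 73% |
| All five, fixed in advance | 4.9% / 5.3% | 95% / 89% |
| Only those with baseline P < .05 | 4.0% / 3.9% | 82% / 74% |
| Smallest P over all 2^5 = 32 covariate sets | 13.9% / 14.2% | not comparable |

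The Monte Carlo standard error is about √(0.05 × 0.95 / 5000) = 0.3 percentage points for type I error. For power near 80% it is about √(0.8 × 0.2 / 2000) = 0.9 points.

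Selection by baseline P is slightly conservative and recovers almost none of the power that fixed adjustment gains. Inflation appears only in the last row, where the choice is made on the result itself.

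The power gap shown (95% against 82%) overstates what could happen here. In the simulation every covariate was at the mercy of the baseline test. In this plan several covariates are named regardless.

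**3. Covariates tied to the arm.** The Yoga Intervention section has certified yoga teachers leading one arm. The control section has physical therapists or other exercise instructors leading the other. If no instructor teaches in both arms, instructor indicators entered as fixed effects add up exactly to the arm indicator, and the arm effect cannot be separated from them. The Essential Properties of Yoga Questionnaire rates both interventions on dimensions such as breathwork and mindfulness. The Objectives section says that only yoga will contain these.

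**The case against.** The strongest reply is that the two sentences are unconnected. The article never says that a baseline test result brings a covariate into a model. A reader might infer that chance imbalances will decide the adjustment of the primary result, and the text does not support this. Sex, race, cohort, instructor and the two questionnaires are adjusted for whatever the tests show, and baseline pain severity is fixed in the mediation model. Nor are baseline tests the only possible route into the list, since the Exploratory Variables section looks at associations with outcome. This part of the reply stands.

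A reader might also infer inflated type I error from imbalance-driven selection. The simulation points the other way.

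It can further be said that this is a condensed article, that an unseen analysis plan may close the list, and that coded arms limit steering towards a favoured treatment. That is fair, and it lowers the weight of the point. But the baseline tests and the open wording are stated procedures, not omissions. Coding the arms hides direction but does not fix the list. Instructor and the yoga-properties ratings could also reveal which code is which.

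**Conclusion.** The point holds as a minor one. The planned baseline tests are uninformative, assuming that allocation works and that baseline measures are taken before participants learn their arm. At least one flagged difference is quite likely: 40% with 10 independent variables and 79% with 30, less with correlation.

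The covariate list for all analyses is open and mixes baseline characteristics with variables tied to the arm or to delivery. Additions could therefore be made after data are seen, though the article does not say that they will be.

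If additions were chosen by baseline P, the main cost would be precision relative to a fixed list. Inflation of the size simulated (about 14%) would need covariates to be chosen on the result. The open wording does not exclude this, but nothing in the article plans it. The simulated figures rest on assumed coefficients, five covariates and d = 0.4, and show direction rather than a forecast for this trial.

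**What to change.** 1. End the baseline sentence at the word *descriptively*, dropping the between-arm tests, and report baseline data by arm.
2. Before unblinding, fix the primary BPI-SF model to a closed set of baseline covariates: baseline BPI-SF, the stratification factor sex, age and cohort.
3. State that no covariate enters or leaves the model because of an observed baseline difference.
4. Label any other adjustment, including instructor, the Essential Properties of Yoga Questionnaire and the Credibility Expectancy Questionnaire, as a sensitivity or mechanistic analysis.

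The cost is one deleted clause and a few added sentences. If an analysis plan already closes the list, it only needs to be cited and brought into line. No data collection or trial procedure changes.

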**Results:**

The primary outcome will be the mean change in pain severity as measured by the Brief Pain Inventory-Short Form at 12 weeks. The primary mechanism of action is ER measured by change in the Difficulties in Emotion Regulation Scale total score. Secondary outcomes include pain sensitivity, physical strength and flexibility, pain interference, and quality of life. A mediation path analysis and series of moderated mediation path analyses will be conducted to test the study hypotheses. As of January 2024, we have enrolled 138 participants. We expect the study to be completed by May 2025.

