#### Primary Outcome: Primary MOA

Pain severity will be measured with the Brief Pain Inventory-Short Form (BPI-SF) [59] at 12 weeks. The BPI-SF has been validated with CLBP and has shown good reliability [60].

ER as the primary MOA will be measured using the Difficulties in Emotion Regulation Scale (DERS) score at 12 weeks. The DERS is the gold standard self-report measure of individuals’ abilities to respond to emotional experiences in a goal-oriented manner [60]. The 36-item DERS taps aspects of difficulties with ER, which we anticipate will lessen with yoga practice [61]. Participants rate the extent to which each of 36 statements currently applies to them, and the measure yields a total score comprising summed subscales. The DERS is sensitive to change over time in ER, and internal consistency reliability is high [60].

The Negative Affective Priming Task [62] will also be used to capture individual differences in emotional attention, reactivity and appraisal, and ability to inhibit negative emotion and purposefully shift attention to more positive aspects of daily life. Participants are exposed to neutral and affective words with a strong positive and negative valence in consecutive paired trials, one word serving as the “target” and the other as a “distractor.” Participants are instructed to ignore the distractor and to attend to the target in both control and negative priming conditions, with “inhibition ability” operationalized as a difference score between response latencies in control and negative priming conditions. The stronger one’s inhibition abilities, the longer the latency in the negative priming condition compared to the control condition (scored in milliseconds). Individuals with chronic depression and greater tendency to engage in maladaptive rumination demonstrate reduced ability to inhibit negative, as opposed to neutral, words with no difference in the ability to inhibit positive words [63,64].

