### Statistical Analysis

The primary aim of this study will test the null hypothesis that the 2 population means are equal between the yoga and stretching and strengthening groups on the primary outcome, pain severity as measured by the BPI-SF, as well as the primary MOA, ER as assessed by the DERS. Power calculations incorporated prior effect sizes from works by others. A proposed sample size of 102 per group, which adjusted for attrition, was calculated to detect statistically significant results with 80% power (estimated *d*=0.50). In consideration of our secondary aims, we also powered the detection of paths a and b within pain interference mediation models. This was done using simulation in R (R Foundation for Statistical Computing; N=5000). Following simulation methods (N=5000) presented in Fritz and MacKinnon [76], sample size was determined by increasing simulation sample size until 90% of simulations significantly detected both paths a and b with estimated effect size magnitudes of *d*=0.39 (path a) and *d*=0.26 (path b) at α=.05. A proposed sample size of 116 was calculated, which was already reached when powering our primary aim.

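### The primary 12-week contrast is worded two ways and tied to no single model; naming one baseline-adjusted analysis would gain precision and remove the inconsistency

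*Protocol article*

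**What the plan says.** **Endpoint.** The Abstract (Results) states: "The primary outcome will be the mean change in pain severity as measured by the Brief Pain Inventory-Short Form at 12 weeks". The Methods section on the primary outcome and primary MOA gives the instrument and the 12-week visit ("Pain severity will be measured with the Brief Pain Inventory-Short Form (BPI-SF") and does not mention change. Within the mediation model in Data Analysis, path b leads to "pain severity (BPI-SF) at 12 weeks (path b) controlling for baseline pain severity", while path c is "the direct path between group and change in pain severity at 12 weeks (path c").

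**Hypothesis and sizing.** Statistical Analysis says the primary aim "will test the null hypothesis that the 2 population means are equal between the yoga and stretching and strengthening groups", for BPI-SF severity and for DERS. It gives no time point and no covariate. The sample size is 102 per group for 80% power at d=0.50, adjusted for attrition; no attrition rate and no baseline correlation are given.

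**Methods.** Data Analysis says that, if assumptions are met, two-sided t "tests, mixed effects models, and path analyses will test our hypotheses". None of the three is assigned to the primary contrast.

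**Covariates.** Baseline pain severity is named as a control only in the mediation model. Baseline DERS appears as a moderator and in a responder comparison. A general sentence adds: "All analyses will also be adjusted for important covariates including, but not limited to demographics", followed by cohort, instructor, intervention components and credibility. The baseline value of the outcome is not in that list, but the list is open.

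**The concern.** The two endpoint wordings and the unassigned methods leave more than one analysis that could be reported as primary: a t test on 12-week scores, a t test on change, or a mixed model with or without baseline. They estimate the same arm difference in expectation, but they have different precision and will give different P values in any one data set.

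The t test is the natural reading of a two-means hypothesis sized by a standardised difference. It also makes the least use of the data. On 12-week scores it ignores baseline. On change scores it uses baseline with a fixed coefficient of 1 rather than the estimated one. At stake are power for the primary outcome and for DERS, and a primary result that does not depend on a later choice among listed methods.

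**Working it through.** **Inputs from the article:** d=0.50, 80% power, 102 per group (Statistical Analysis); two-sided tests, α=.05 (Data Analysis).

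**Assumptions not in the article:** correlation r between baseline and 12-week BPI-SF severity, taken as 0.4 to 0.6 and checked over 0.3 to 0.8; equal SDs at both visits.

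**1. The plan's own figure.** With the normal approximation, n per arm = 2(1.960 + 0.842)² / 0.50² = 62.8, so 63. The exact two-sample t test gives 63.8, so 64. Getting from 64 to 102 needs attrition of 1 − 64/102 = 37%. As no rate is stated, 102 can be neither confirmed nor refuted. What the calculation shows is that the sizing has the form of an unadjusted comparison of two means. With all 102 per arm evaluable, the same t test has about 94% power.

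**2. Relative variance of the arm difference** (12-week-score t test = 1):
- change-score t test: 2(1 − r)
- ANCOVA on baseline: 1 − r²
- ANCOVA relative to change score: (1 − r²) / [2(1 − r)] = (1 + r)/2

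Both 1 − r² and (1 + r)/2 are at most 1, so apart from the degree of freedom spent ANCOVA is never less precise than either t test.

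**3. Results**, with power at 64 evaluable per arm and a difference of 0.50 in 12-week SD units:

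| r | Change var. | ANCOVA var. | ANCOVA / change | Power, 12-week t | Power, change t | Power, ANCOVA |
|---|---|---|---|---|---|---|
| 0.3 | 1.40 | 0.91 | 0.65 | 80.1% | 66.0% | 83.7% |
| 0.4 | 1.20 | 0.84 | 0.70 | 80.1% | 72.7% | 86.5% |
| 0.5 | 1.00 | 0.75 | 0.75 | 80.1% | 80.1% | 90.0% |
| 0.6 | 0.80 | 0.64 | 0.80 | 80.1% | 88.1% | 93.9% |
| 0.7 | 0.60 | 0.51 | 0.85 | 80.1% | 95.2% | 97.6% |
| 0.8 | 0.40 | 0.36 | 0.90 | 80.1% | 99.3% | 99.7% |

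For r from 0.4 to 0.6, ANCOVA variance is 16-36% below the 12-week t test and 20-30% below the change-score t test.

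**4. The endpoint wording matters if a t test is used.** The change-score test is less precise than the 12-week test below r=0.5 and more precise above it. Power at 64 per arm is 73% against 80% at r=0.4, and 88% against 80% at r=0.6. Once baseline is a covariate, a linear model for change and one for the 12-week score give the same arm difference, so the two wordings no longer compete.

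**5. If d=0.50 is in change-score SD units instead** (the article does not say), ANCOVA at 64 per arm has 91.8%, 90.0% and 88.1% power for r=0.4, 0.5 and 0.6, against 80.1% for the change-score t test.

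**The case against.** The strongest reply is that the article does not commit to an unadjusted t test. Three families of method are listed and none is assigned to the primary contrast. A change score contains the baseline, a mixed model may include it, and the covariate sentence is open-ended, so it does not exclude baseline severity. Baseline DERS would normally enter as a main effect where it is examined as a moderator, and the mediation model already controls for baseline pain. All of this stands.

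It follows that some stronger readings are not supported:
- A reader might infer that the primary test is a t test that ignores baseline. The text permits this but does not state it.
- A reader might infer that participants with 6-week but no 12-week data will be discarded. That holds only if the t test is used; the listed mixed model could retain them.
- A reader might infer bias. Under randomisation either t test is unbiased and keeps its type I error; chance baseline imbalance costs precision.

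The reply also says that model choice and covariates belong in an analysis plan that is not shown. Missing model detail in an article is indeed no finding. What remains is stated text that does not agree with itself: change against 12-week value, and t tests against adjustment of all analyses. An open list may allow baseline adjustment but does not fix it.

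Finally, the power figures rest on 64 evaluable per arm. With all 102 retained the t test already has about 94%, so at most about 6 percentage points are left to gain.

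**Conclusion.** The point holds as a matter of precision and consistency, not validity. The primary endpoint has two wordings, no method is assigned to its test, the hypothesis and sizing fit a t test that cannot meet the all-analyses-adjusted statement, and baseline severity is explicitly controlled only for mediation.

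The direction of the gain does not depend on the assumed correlation: apart from the degree of freedom spent, a baseline-adjusted model is at least as precise as either t test at every r. Its size does. The 16-36% and 20-30% variance reductions rest on r of 0.4 to 0.6 and equal SDs. The rise from 80% to about 87-94% power also needs 64 evaluable per arm and d in 12-week SD units. The article gives none of these. The change is worth making because it improves precision with data already collected.

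**What to change.** Name one primary analysis: an ANCOVA or a mixed model for BPI-SF severity, with the yoga-minus-stretching difference at 12 weeks as the estimate, adjusted for baseline BPI-SF severity and for sex, the randomisation stratum. Use the same model for DERS with baseline DERS. Drop the t tests for these two contrasts, which also removes the conflict with the covariate statement. Word the endpoint identically in the Abstract, the primary outcome section, Statistical Analysis and Data Analysis.

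The cost is analysis wording and a degree of freedom or two. Baseline BPI-SF and DERS are already collected, and the article plans no interim analysis of the primary and secondary outcomes and no analysis before final data collection, so the choice can be fixed before analysis.
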